### Study design

This will be a clustered randomised controlled trial with multiple data collection points.

Data will be collected from 360 Italian pharmacists who will provide I-MUR services to 1800 patients over a nine-month period.

A standard randomised study design would mean that some pharmacists would not provide the I-MUR service to their patients, in order to form a control group, an approach which could lead to demoralise and disengage pharmacists who will not have the chance to provide the service. In addition, individual pharmacists may differ in their practices, and their patients may be cared for by GPs with different practices. Hence the study design must minimise the impact of any individual pharmacist or GP on the management of asthma. To avoid these problems, it was decided to design a cluster randomised control trial in which pharmacists are randomly allocated to provide the intervention to their patients either early or later during the study period. Randomisation will be at pharmacist level, not at patient level, with each pharmacist representing a cluster and outcome being measured for individuals within those clusters [26].

Data will be collected before, during and after intervention delivery, to assess if timing of the intervention affects the primary outcome: the severity of asthma.

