#### Planned intervention

Pharmacists will provide the I-MUR service following administration of the ACT at either T0 or T3 depending on group allocation, recording details of all PCIs identified and advice provided during the I-MUR consultation.

The I-MUR intervention covers the following areas: patients’ demographics, their regular medications (active ingredients) including those used for asthma, patients’ attitude towards their medications and adherence to treatments assessed with the I-MUR interview, pharmaceutical care issues identified by the pharmacist, pharmacist’s advice given to patients, including healthy living advice, pharmacist’s advice given to Doctors, pharmacist’s own view on the potential benefit to the patient of the MUR service they provided.

Following each consultation, pharmacists will be required to enter the results into the web-based template provided, maintaining patient anonymity.

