### Pharmacist training

Training sessions will last for a half day and will be provided in each region by the PI, a fully trained and qualified pharmacist accredited to provide MURs in England since 2005. The training supports the development of pharmacists’ clinical skills and knowledge using question and answer sessions, mock interviews and role-play. The training material was developed and evaluated during earlier work. Contributions to the training will also be included from local respiratory consultants and general practitioners who will cover asthma management, physiopathology, medical conditions, different treatments according to asthma severity and GINA guidelines. Pharmacists from Groups A and B will be trained at different times. The use of the ACT test will be explained to both groups before T0 but only group A will receive the I-MUR training at this time point; group B will receive this training just before T3.

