### Proposed sample size

It is aimed to obtain a final sample size of 360 pharmacists and 1800 patients, requiring each pharmacist to provide the intervention to five patients. The power calculation for this study has been conducted taking into consideration the intra-cluster and inter-cluster correlation (ICC) using SPSS sample power calculation. The ICC represents the correlation between responses of individuals in the same clusters which is a proportion of the total variation explained by variation between clusters [28] and its value ranges between 0 and 1. For this study it was decided to use an ICC = 0.02 as this was used in a similar study conducted in Australia [17]. This is based on an estimated 20% difference in asthma severity (ACT score), which may be achieved, again based on the Australian study [17], which found that the proportion of patients classified as having severe asthma declined from 87.9% to 52.7% following pharmacist intervention. This is based on an anticipated 40% improvement in asthma severity following pharmacist intervention; the difference will be measured by comparing the ACT score gathered at baseline to T3, T6, T9 for each patient, where an ACT score ≤ 19 means not well controlled asthma and an ACT score ≥ 20 well controlled asthma.

Four options were considered (Table 1) all using d = 20% and alpha = 0.05, but considering different numbers of pharmacists and patients per pharmacy. Option d was chosen, as it has a power of 95%. The calculated ratio between pharmacists and patient in order to achieve the above results is 1:4. The attrition rate was estimated as 23% based on the Australian study, which had an attrition rate of 14%, but following which the authors suggested that this percentage could be in the range of 14-25% [17]. Therefore pharmacists will be required to recruit five patients instead of four. Based on an attrition rate of 23%, 396 patients will not complete the study, leaving 1386, which is still sufficient to attain option d (693 patients per group).

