### Data analysis

In studies where the important baseline factors seem well balanced, it is likely that any differences in outcome between intervention and control groups are a real effect of treatment, which is one component of the internal validity. Patients’ location, age, gender and ACT score will be collected and compared at baseline. This baseline ACT score will provide information regarding the level/severity of asthma prior to intervention delivery.

Quantitative data gathered through the web platform (Qualtrics^©^) will be exported and analysed using SPSS version 22. Patient location, age, gender and ACT score will be compared at baseline.

Asthma severity assessed by ACT score will be analysed over time within individual patients to obtain a percentage change score. Scores will be compared between groups at all times points. The number of active ingredients in use and reported adherence to treatment will be compared at three time points after provision of the I-MUR. The number of PCIs identified and advice given by pharmacists will be captured for both groups separately and combined. Any change in the severity of asthma and the accompanying percentage variation in cost (based on peer reviewed published data) will also be assessed. It will be possible to compare data before and after the I-MUR intervention for group A and B, separately and combined. In addition findings will be analysed by region.

A significance level (alpha) of 0.05 will be used in all analyses. Between-group differences at baseline will be compared using independent Student’s t-test for continuous parameters and Pearson’s χ^2^ will be used for categorical parameters. Outcomes for continuous parameters will be evaluated using repeated measures multivariate ANOVA.

The analysis will be conducted in two steps. Step one will represent an interim analysis after the first six months, after completion of T6, by which time all patients will have been followed up for three months after the intervention. Step two will represent the final analysis, which will be conducted at the end of the study after T9.

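### Only T3 compares I-MUR with no I-MUR under randomisation, but the plan measures the effect as within-patient change and names no deciding comparison

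*Protocol article*

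**What the plan says.** All places are in the Protocol article.

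- **Allocation (Study design):** "pharmacists are randomly allocated to provide the intervention to their patients either early or later during the study period". The same section gives the reason for repeated data collection: to see whether timing of the intervention affects asthma severity.
- **Timing (Planned intervention):** "Pharmacists will provide the I-MUR service following administration of the ACT at either T0 or T3 depending on group allocation".
- **Training (Pharmacist training):** "only group A will receive the I-MUR training at this time point; group B will receive this training just before T3".
- **Effect definition (Proposed sample size):** "the difference will be measured by comparing the ACT score gathered at baseline to T3, T6, T9 for each patient".
- **Comparisons (Data analysis):** a within-patient percentage change in ACT is derived. Then "Scores will be compared between groups at all times points", and "It will be possible to compare data before and after the I-MUR intervention for group A and B, separately and combined". Continuous outcomes go to a repeated measures multivariate ANOVA.
- **Error rate and steps (Data analysis):** "A significance level (alpha) of 0.05 will be used in all analyses". "Step one will represent an interim analysis after the first six months", and a final analysis follows T9.
- **Primary outcome:** asthma severity by ACT before, during and after the service. No visit or contrast is singled out.

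The first principal research question is whether the I-MUR is effective in reducing asthma severity.

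**The concern.** The design yields one randomised answer to the effectiveness question, at T3. By T6 and T9 both groups have had the service. If the I-MUR works and Group B catches up, no group difference is expected at those visits.

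The stated effect measure is not that randomised contrast. It is change from baseline within each patient, and it counts season, regression to the mean and any other drift as effect. Pooling A and B before and after the I-MUR does not remove such drift.

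The randomised T3 comparison is planned, but only as one unranked item among several group comparisons and before/after comparisons, each at 0.05. A claim of effectiveness could therefore rest on an uncontrolled change, or on whichever comparison turned out significant. The article expects the results to inform national policy on the service, so it matters which comparison carries the claim.

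**Working it through.** **1. Which visits compare I-MUR with no I-MUR?** From Planned intervention and Pharmacist training, with each I-MUR given after that visit's ACT:

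| ACT at | Group A | Group B | What A versus B estimates |
|---|---|---|---|
| T0 | before I-MUR | before I-MUR | baseline balance |
| T3 | 3 months after | before I-MUR | I-MUR versus none |
| T6 | 6 months after | 3 months after | early versus later |
| T9 | 9 months after | 6 months after | early versus later |

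**2. The plan's own sample size.** Inputs from Proposed sample size and Table 1, option D: d = 20%, read as 0.20 SD; alpha 0.05, taken as two-sided; power 95%; ICC 0.02; 4 patients per pharmacist.

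- Unclustered n per group = 2 × (1.960 + 1.645)² / 0.20² ≈ 650.
- Design effect = 1 + (4 − 1) × 0.02 = 1.06.
- n per group = 650 × 1.06 = 689, against 693 stated.
- Power at 693: effective n = 693 / 1.06 = 653.8; standard error = √(2 / 653.8) = 0.0553; 0.20 / 0.0553 = 3.616; power = Φ(3.616 − 1.960) = 95.1%.

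Options A, B and C also reproduce (568, 558 and 702, against 575, 560 and 700 stated). One-sided alpha gives about 575 for option D. A 20-point difference in proportions gives about 116 to 170 per group for the starting proportions tried. Neither fits. The trial is sized for a two-group difference, and for I-MUR versus none only T3 supplies one.

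**3. What an uncontrolled change can show.** Assume no I-MUR effect, a drift of 0.10 SD, visit correlation ρ and design effect 1.06. The drift and ρ are assumptions; the documents give neither. The standard error of mean change is √(2(1 − ρ)) × √(1.06 / n).

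| ρ | Significant before/after, n = 693 | n = 1386 (pooled) |
|---|---|---|
| 0.5 | 72% | 95% |
| 0.7 | 91% | 99.7% |

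With a drift of 0.05 SD the figures are 25-38% and 44-65%.

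**4. Multiplicity.** Three group tests (T3, T6, T9), each at two-sided 0.05, with no true difference. If independent: 1 − 0.95³ = 14.3%. With test statistics correlated 0.4, 0.5, 0.6 and 0.7 (assumed, by simulation): about 13%, 12.5%, 12% and 11%.

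**5. Does the named repeated measures method lose power?** Assume a true difference of 0.20 SD at T3 only, so (0, 0.20, 0, 0) over T0-T9, with equal visit correlations ρ. For the group-by-time term (3 df), the noncentrality is (653.8 / 2) × Σ(δ − mean δ)² / (1 − ρ). The mean δ is 0.05, and the sum is 0.15² + 3 × 0.05² = 0.03. This gives 9.81 / (1 − ρ), or 16.3 at ρ = 0.4 and 32.7 at ρ = 0.7. Power is about 94% to 99.9%. T3 adjusted for T0 (variance factor 1 − ρ²) gives about 98% to 99.9%.

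**The case against.** **The T6 and T9 comparisons have a stated purpose.** This stands. They remain randomised, early against later, and they serve the timing aim in Study design. They are not errors; they do not answer the effectiveness question.

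**The T3 contrast is already planned, and the before/after sentence is only permissive.** Both are true, so the randomised answer is not absent. But the sample size section states outright how the difference will be measured, and that measure is within patients. Nothing ranks T3 above it.

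**A condensed article leaves model terms and multiplicity to the analysis plan.** This is fair for the model term and for details of adjustment. It does not cover an effect definition that the article itself fixes, and fixes at odds with its own sample size.

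**A reader might infer that the repeated measures analysis dilutes the effect.** The group main effect averaged over four visits would have only 18-23% power under the assumptions in step 5. The documents do not name that term as the test. The group-by-time term, the natural one for change over time, keeps about 94-99.9%. What remains is narrower: the article does not say which term decides, and a 3-df interaction responds to divergence at any visit, so it does not isolate T3.

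**A reader might take the error inflation as certain.** It is conditional. The multivariate ANOVA could supply one omnibus test, and the article does not say that each visit is a separate confirmatory test. Likewise, two steps at 0.05 give about 8-9% (correlations 0.5-0.8) only if success may be claimed at either step. No stopping rule or success claim is attached to step one, and T3 data are complete by then, so T3 is not re-tested on accruing data.

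**Conclusion.** The point holds, and should be settled before analysis. T3 is the only randomised I-MUR versus no I-MUR comparison after baseline. The stated effect measure is uncontrolled within-patient change, which conflicts with a sample size that reproduces as a two-group difference of 0.20 SD (689 against 693 per group; 95.1% power). No comparison is named as decisive.

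The familywise error of about 11-13% rests on assumed correlations of 0.4-0.7 and on T3, T6 and T9 each being able to support a success claim. The before/after figures rest on an assumed drift; they show sensitivity and do not predict what will occur. ACT is not an entry criterion, so the size of any regression to the mean is unknown.

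The documents do not support a claim that the planned method lacks power, or that the T6 and T9 comparisons are invalid.

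**What to change.** In Proposed sample size and Data analysis:

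1. State one primary test: the A versus B difference in ACT at T3, with Group B's score taken before its I-MUR as Planned intervention already orders it. Adjust for T0 ACT, allow for clustering by pharmacist, use two-sided 0.05, and test it once.
2. Replace the effect definition by patient in Proposed sample size with this between-group difference.
3. Label the T6 and T9 group comparisons as secondary, for timing and maintenance.
4. Label all before/after results, separate or combined, as descriptive.

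The change is to wording. It needs no extra patients or visits, since 693 per group gives about 95% power at T3 even before baseline adjustment. The cost is that T6, T9 and pooled before/after results carry no confirmatory claim of effectiveness.

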An Australian multi-site randomised controlled trial compared pharmacist counseling on asthma, asthma medication and associated lifestyle advice with a control group providing usual care. Fifty pharmacies were enrolled and randomly allocated to one of the two groups (randomisation conducted at pharmacy level), the intervention group with 191 patients and the control group with 205 patients. In both groups questionnaires and spirometric testing were carried out at baseline and at six months. The main outcome measure was asthma severity/control status assessed by a tool adapted from the National Asthma Council. The percentage of patients in the intervention group classified as having severe asthma declined from 87.9% to 52.7% (p < 0.01), whilst the change in the control group the change was not significant (71.2% to 67.9%; p = 0.11). These authors used a multilevel logistic regression model to adjust for the difference in asthma severity at baseline and to account for any possible effect from clustering. Both pharmacist groups administered questionnaires and spirometric testing at baseline and six months later; it was found that patients in the intervention group were almost three times more likely to change from the severe asthma category to the not severe category than patients in the control group (OR 2.68, 95% CI 1.64 to 4.37 p < 0.01) [17].

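### The analysis named for ACT and other continuous outcomes, repeated measures MANOVA, ignores clustering by pharmacist, although pharmacists are randomised and the sample size allows for it

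*Protocol article*

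**What the plan says.** Under Study design, the article fixes the unit of allocation: "Randomisation will be at pharmacist level, not at patient level, with each pharmacist representing a cluster". Under Proposed sample size, it carries this into the calculation: "For this study it was decided to use an ICC = 0.02 as this was used in a similar study conducted in Australia". Table 1 lists four options, "all using d = 20% and alpha = 0.05", and the text selects the last: "Option d was chosen, as it has a power of 95" per cent. Option D has 173 pharmacists and 693 patients per group at a ratio of 1:4.

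Under Data analysis, the one method named for continuous outcomes is: "Outcomes for continuous parameters will be evaluated using repeated measures multivariate ANOVA". The independent t-test is assigned to baseline differences, and Pearson's chi-square follows in the same sentence. For this trial the article mentions no pharmacist effect, multilevel or mixed model, GEE, robust variance or cluster-level summary.

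The background section on pharmacists' role in asthma management describes the Australian trial that supplied the ICC: "These authors used a multilevel logistic regression model to adjust for the difference in asthma severity at baseline". The same sentence says that the model also dealt with clustering.

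**The concern.** Patients of one pharmacist share a trainer, a counsellor and often a local medical practice, so their scores can be correlated. A patient-level repeated measures MANOVA treats each patient as an independent unit. Its repeated-measures structure concerns time within a patient and does nothing for similarity between patients of the same pharmacist. If that similarity is present, the variance of a difference between groups is understated, p-values are too small and confidence intervals too narrow.

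The comparison most exposed is the one the trial most needs. Under Planned intervention, group B receives the I-MUR after the ACT at T3, so the groups at T3 are the last comparison with an untreated control. The article also sizes the trial under one variance model and analyses it under another. It took its ICC from a trial that used a multilevel model, but did not take the model.

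**Working it through.** **Inputs.** From Proposed sample size and Table 1: ICC 0.02; alpha 0.05; power 95%; 4 patients per pharmacist in the calculation ("The calculated ratio between pharmacists and patient in order to achieve the above results is 1:4"), 5 recruited; 693 patients per group after attrition. Two readings are assumed because they reproduce the table: alpha is two-sided, and d = 20% is a standardised difference of 0.20. Read as 20 percentage points between two proportions, d would need only about 116–180 patients per group.

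**Step 1: does the sample size include clustering?**
- Unclustered n per group = 2(1.96 + 1.645)² / 0.20² = 650.
- Design effect DE = 1 + (m − 1) × ICC = 1 + 3 × 0.02 = 1.06.
- 650 × 1.06 = 689. In whole clusters of 4 this is 173 pharmacists and 692 patients, against 173 and 693 stated.
- The same formula gives 570, 560 and 705 for options A, B and C, against 575, 560 and 700 stated.

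The table reproduces, so the sample size does include clustering.

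**Step 2: what happens if the analysis leaves it out?** For groups compared at one time point:
- true SE = naive SE × √DE, so the naive SE is too small by 1 − 1/√DE;
- actual two-sided alpha = 2 × [1 − Φ(1.96/√DE)].

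| ICC | Patients per pharmacist | DE | SE too small by | Actual alpha |
|---|---|---|---|---|
| 0.02 (protocol) | 4 | 1.06 | 2.9% | 0.057 |
| 0.02 (protocol) | 5 | 1.08 | 3.8% | 0.059 |
| 0.05 (assumed) | 4 | 1.15 | 6.7% | 0.068 |
| 0.05 (assumed) | 5 | 1.20 | 8.7% | 0.074 |
| 0.10 (assumed) | 4 | 1.30 | 12.3% | 0.086 |
| 0.10 (assumed) | 5 | 1.40 | 15.5% | 0.098 |

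The average cluster left after attrition is 1386/360 = 3.85 patients. At ICC 0.02 this gives DE 1.057 and alpha 0.057, so the 4-per-pharmacist rows fit the analysed data.

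**Step 3: check by simulation.** With no true effect, 173 clusters of 4 per group and 20,000 runs per ICC, a patient-level test rejected in 5.7%, 6.4% and 8.9% of runs at ICC 0.02, 0.05 and 0.10. A test on cluster means rejected in 5.0%, 4.7% and 5.3%. The simulation error is about 0.15–0.2 percentage points, so both agree with the formula.

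**Step 4: does a correct analysis need more patients?** The effective size is 693/1.06 = 654 per group. Power = Φ(0.20 × √(654/2) − 1.96) = Φ(1.66), about 95.1%. No increase is needed.

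**The case against.** The strongest objection is that the alpha formula may not describe the test that will be reported. The article also analyses ACT as change within patients. In a group-by-time test, any pharmacist difference that is constant over time cancels, and only pharmacist-level variation in change inflates the error. This stands: the figures above apply to a comparison at one time point, and the ICC of change is not given. It does not remove the point. Pharmacists deliver the intervention, so change may cluster too, and the article also compares groups at each time point.

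Second, allocation is stratified by region. Any part of the ICC due to region is balanced by design and does not inflate the comparison of groups. This also stands, and is a reason to put region in the model.

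Third, such detail might be left to an analysis plan. That would answer an omission, but here a method is named and it does not fit the design.

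Fourth, the effect at ICC 0.02 is modest. That is correct.

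Three stronger readings are tempting but not supported:
- A reader might infer that t-tests and chi-square tests are the outcome analyses. The t-test is stated for baseline differences, and the chi-square shares that sentence, so these tests are not the main problem.
- A reader might infer error rates of 12% or more for adherence or number of ingredients. That needs an ICC of 0.2 or higher, for which the article gives no basis. It also describes those two outcomes as patient-reported and compared over time after the I-MUR.
- A reader might treat loss of patients with a missing visit as a separate fault. The article states no complete-case rule, handling of missing data may sit in an analysis plan, and the sample size already allows for 23% attrition.

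**Conclusion.** The point holds for the MANOVA. The named analysis of the primary outcome matches neither the unit of randomisation nor the variance model behind the sample size, and its between-group standard errors are too small. At the protocol's own ICC the excess over the nominal 0.05 is under one percentage point for a comparison at one time point, so this alone is unlikely to reverse a clear result. It grows if the ICC is larger. The value of 0.02 is borrowed from another country, and the article says that no other Italian asthma work with community pharmacists exists, so the higher ICCs in the table are assumptions to show the range and not estimates. For group-by-time effects the direction is the same wherever change varies between pharmacists, but the size cannot be given. The article should be corrected because a method that contradicts the design is written down and the correction is cheap.

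**What to change.** Replace the MANOVA sentence with wording such as: ACT will be analysed with a linear mixed model with fixed effects for group, visit, group-by-visit and region, random effects for pharmacist and pharmacist-by-visit, and a within-patient covariance across visits; group differences will be estimated at each visit from this model. The pharmacist-by-visit term is needed because a pharmacist intercept alone covers only differences that stay constant over time. Use the same structure for other continuous outcomes compared between groups. If the split at ACT ≥ 20 is tested between groups, use a multilevel logistic model or GEE clustered on pharmacist.

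A side benefit is that the mixed model uses every available visit, whereas a standard repeated measures MANOVA uses only patients with all visits.

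The cost is a change of wording and slightly wider intervals: at ICC 0.02, by a factor of √1.06 = 1.03 to √1.08 = 1.04. Recruitment targets do not change.

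### The trial randomises pharmacists, but the analysis named for continuous outcomes, including the primary ACT score, treats patients of the same pharmacist as independent

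*Protocol article*

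**What the plan says.** Three parts of the protocol article bear on this.

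- **Design.** The Study design section makes the pharmacist the unit of allocation: "Randomisation will be at pharmacist level, not at patient level, with each pharmacist representing a cluster and outcome being measured for individuals within those clusters".
- **Sample size.** The Proposed sample size section allows for clustering: "For this study it was decided to use an ICC = 0.02 as this was used in a similar study conducted in Australia". All four options in Table 1 use that value. The chosen option D has 173 pharmacists and 693 patients per group, four patients per pharmacist, and 95% power.
- **Analysis.** The Data analysis section assigns Student's t-test to between-group differences at baseline, with Pearson's chi-square for categorical variables in the same sentence. For outcomes it says only: "Outcomes for continuous parameters will be evaluated using repeated measures multivariate ANOVA". It adds: "A significance level (alpha) of 0.05 will be used in all analyses". It also plans to compare ACT scores between the groups at every time point. No random effect, multilevel model, clustered variance or cluster-level summary appears.

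The only multilevel model in the article is in the Background. It was used by the Australian trial from which the ICC was taken, partly "to account for any possible effect from clustering".

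**The concern.** The repeated measures part of the named method deals with the several scores of one patient. It does not deal with the likeness of the four or five patients recruited, tested and counselled by one pharmacist. An analysis that ignores this counts 693 patients per group as 693 independent observations, where the sample size counts them as about 654. Standard errors are then too small, confidence intervals for the ACT effect too narrow, and the stated 0.05 level is not held.

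This is more than detail left to an analysis plan. The article commits to a specific method for the primary outcome, and that method conflicts with its own design and sample size. An analysis plan that followed the sentence would be wrong for the design. One that departed from it would contradict the published protocol.

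**Working it through.** **Inputs from the article:** alpha 0.05, ICC 0.02, d = 20%, power 95%, 693 patients per group, four patients per pharmacist analysed and five recruited. **Assumptions, not in the article:** two-sided testing, ICCs of 0.05 and 0.10, equal cluster sizes, and the correlations over visits used in step 3.

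**1. Reproduce Table 1.** Read d as 0.20 standard deviations. The design effect is DE = 1 + (m − 1) × ICC, with m patients per pharmacist.

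- Unclustered size for 95% power: n = 2 × (1.960 + 1.645)² / 0.20² = 650 per group. For 90% power it is 526.
- DE = 1 + 3 × 0.02 = 1.06 for m = 4, and 1 + 4 × 0.02 = 1.08 for m = 5.

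| Option | n × DE | Stated |
|---|---|---|
| A | 526 × 1.08 = 568 | 575 |
| B | 526 × 1.06 = 558 | 560 |
| C | 650 × 1.08 = 702 | 700 |
| D | 650 × 1.06 = 689 | 693 |

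All agree within 3%. For option D, 693 / 1.06 = 654 effective patients per group, which gives 95.1% power. The planned size therefore already includes clustering.

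**2. Between-group contrast at one visit, clusters ignored.** The standard error is too small by 1 − 1/√DE. The actual level is 2 × [1 − Φ(1.96/√DE)].

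| ICC | m | DE | SE too small by | Actual type I error |
|---|---|---|---|---|
| 0.02 (plan) | 4 | 1.06 | 2.9% | 5.7% |
| 0.02 (plan) | 5 | 1.08 | 3.8% | 5.9% |
| 0.05 (assumed) | 4 | 1.15 | 6.7% | 6.8% |
| 0.05 (assumed) | 5 | 1.20 | 8.7% | 7.4% |
| 0.10 (assumed) | 4 | 1.30 | 12.3% | 8.6% |
| 0.10 (assumed) | 5 | 1.40 | 15.5% | 9.8% |

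A contrast averaged over the four visits is close to this. If pharmacist effects correlate over visits as strongly as a patient's own scores do, the ICC of the average is again 0.02 and the table applies. If they are fully stable and the within-patient correlation is 0.6, the variance of a patient's mean is (1 + 3 × 0.6)/4 = 0.7. The ICC of the average is then 0.02/0.7 = 0.029, DE is 1.086 for m = 4, and the level is 6.0%.

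**3. Group-by-time test over T0, T3, T6 and T9 (3 degrees of freedom).** What matters here is the ICC of change. Let r be the correlation of a pharmacist's effects between visits, and take the within-patient correlation as 0.6. Then ICC of change = 0.02 × (1 − r)/(1 − 0.6) = 0.05 × (1 − r), and the level is P(χ²₃ > 7.815/DE). With m = 4:

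| r | ICC of change | DE | Actual type I error |
|---|---|---|---|
| 1 (constant) | 0 | 1.000 | 5.0% |
| 0.5 | 0.025 | 1.075 | 6.4% |
| 0 (uncorrelated) | 0.05 | 1.15 | 7.9% |

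**4. Simulation of the named method.** With no true effect, 173 clusters of four per group, four visits, both correlations over visits set at 0.5 and 10,000 runs, the group-by-time test rejected in 4.8% of runs at ICC 0, 5.5% at 0.02, 8.4% at 0.05 and 11.4% at 0.10. The step 3 formula gives 5.0%, 6.1%, 7.9% and 11.1% for the same settings. Direction and size agree.

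**The case against.** The strongest case on the other side is that the harm is small where the documents allow it to be measured. At ICC 0.02, standard errors are about 3% too small and a single contrast runs at 5.7%. Ignoring the region strata could offset part of that, though the article gives no figure to size it. The article is condensed, and an unseen analysis plan might add a pharmacist term. The point about size stands. The last does not answer the concern, because the article names a method and does not merely stay silent.

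Three stronger readings are tempting, and the documents do not support them.

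- **That every named test invalidates the conclusions.** The t-test is tied to baseline comparisons, and the chi-square appears to be as well. Neither carries an efficacy conclusion.
- **That the group-by-time test is always hit harder than a single-visit contrast.** A constant pharmacist effect cancels out of change over time, and that test then stays at 5.0%. It fares worse only when pharmacist effects are sufficiently unstable between visits, on which the article gives nothing.
- **That secondary outcomes suffer far larger errors because the pharmacist is the measuring instrument.** Active ingredients and adherence are patient-reported. Pharmaceutical care issues are identified by the pharmacist, but no between-group test is named for them, and the article offers no basis for a high ICC there.

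**Conclusion.** The concern holds. The article fixes, for the primary outcome, a method that ignores the unit of randomisation its own sample size allows for. At the planned ICC the excess error is modest: 5.7–5.9% for a single-visit contrast, and 5.0% to about 7.9% for group-by-time with four patients per pharmacist and an assumed within-patient correlation of 0.6. It becomes marked only if the true ICC is 0.05 or more. The article gives no evidence that it is. However, the 0.02 was borrowed from a trial that measured asthma severity with a different tool, and the named analysis offers no protection if it proves too low. The defect lies in the primary analysis and should be corrected before the data are analysed. It does not show that the trial is too small.

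**What to change.** In the Data analysis section:

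- Replace repeated measures multivariate ANOVA with a linear mixed model containing group, visit and group-by-visit terms, a random pharmacist effect, within-patient correlation over visits, and the region strata. An equivalent analysis clustered on pharmacist would also serve.
- Account for pharmacist in any between-group test of the other outcomes. The choice of count model, and whether to add a pharmacist-by-visit effect, can be left to the analysis plan.
- Use a small-sample correction in the by-region analyses. With 360 pharmacists in 15 regions there are on average 24 per region, or 12 per group. An uncorrected robust test simulated at that size and ICC 0.02 rejected a true null in 7.6% of runs, worse than the problem being fixed.
- Report the observed ICC for each outcome.

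**Cost.** The change takes a few lines of text. At ICC 0.02 intervals widen by about 3% (√1.06 = 1.030), and no extra patients are needed, because 693 per group already includes the design effect. If the ICC is larger, the honest analysis shows the loss: with four patients per pharmacist, power at 693 per group is about 93.5% at ICC 0.05 (693/1.15 = 603 effective) and 90.4% at 0.10 (693/1.30 = 533 effective).
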